### Methods in analysis to handle protocol non-adherence and any statistical methods to handle missing data {20c}

The populations for analysis relating to protocol non-adherence will be defined as the following:Intent-to-treat (ITT): all patients consented who undergo ureteroscopy, complete a baseline PROMIS® Pain Interference questionnaire and fit the definition of an eligible ureteroscopy at the end of the procedure.Pain Modified Intent-to-Treat (PmITT): all patients consented who undergo ureteroscopy, complete a pre-surgery and days 7–10 PROMIS® Pain Interference questionnaire and fit the definition of an eligible ureteroscopy at the end of the procedure.Healthcare Utilization Modified Intent-to-Treat (HCUmITT): all patients consented who undergo ureteroscopy, complete a baseline PROMIS® Pain Interference questionnaire, fit the definition of an eligible ureteroscopy at the end of the procedure, and have complete healthcare utilization data collection for 30 days after the procedure.

For the planned ITT analyses, multiple imputation will be used to address missing data. The details for multiple imputation will be described fully in the statistical analysis plan.

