## Assignment of interventions: allocation

### Sequence generation {16a}

Participants in the randomization cohort will be randomized intraoperatively using an online computer-based system (https://randomize.net/) to either stent omission or stent placement in a 1:1 ratio. This will take place after the completion of the lithotripsy portion of the procedure and verification of second-stage eligibility by the operating urologist. Blocked, stratified randomization based upon surgeon-classified stone location (renal only versus ureteral with or without renal), with random block sizes will be used to ensure group balance.

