## Assignment of interventions: blinding

### Who will be blinded {17a}

The operating urologist will need to perform the allocated treatment (stent omission or stent placement) and therefore cannot be blinded. Because the presence of a stent necessitates arrangements need to be made for future stent removal, patients will also be informed of the presence or absence of a stent immediately following their surgery and will not be blinded.

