### Plans to promote participant retention and complete follow-up {18b}

Participation in the SOUL study is short-term, and minimal loss to follow-up is expected. Follow-up is limited to only routine postoperative clinical care, and no study-specific visits or tests are required.

Patients will receive PRO surveys electronically via an automated system. If a patient does not log-in or fails to complete the preoperative PRO survey, they will receive an electronic automated reminder and will be contacted by the MUSIC Coordinating Center. If a patient does not log-in or fails to complete the 7-day survey, they will receive an electronic automated reminder and will be contacted by the MUSIC Coordinating Center to facilitate its completion by the end of post-operative day 10. The SOUL Study Team may also administer the PRO questionnaires via REDCap, phone, or paper if the participant is unable to complete surveys through the MUSIC Registry. Similar procedures will be used for the completion of the 4–6-week PRO surveys.

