#### Randomized cohort analysis

A linear (ANCOVA) model will be used on the intention to treat (ITT) population to compare the two treatments, with PROMIS Pain Interference *t*-score at postoperative days 7–10 as the dependent variable and treatment group, stratification factor (stone location [kidney or ureter]) and pre-surgery (baseline) Pain Interference *t*-score as the independent variables [33]. The adjusted parameter estimate for treatment group (stent omission vs. placement) will be reported with the associated 97.5% CI and *p*-value (based on a type 3 *F*-test) that allows testing the hypothesis that Pain Interference differs between the two treatment groups. Multiple imputation will be used to address missing data and will be described fully in the statistical analysis plan. Sensitivity analysis will be conducted with the same analysis in the pain-modified intent-to-treat (PmITT, see Sect. 20c) population to assess the robustness of the effect found in the primary analysis. Additional sensitivity analysis will be conducted if there is baseline imbalance.

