#### Randomized cohort analysis

The analysis of the hierarchical composite endpoint of healthcare utilization using the Win Ratio [29] in the RCT will use the ITT population and will use the unmatched approach [35, 36]. The composite healthcare utilization metric within 30 days will be an assigned score for each patient based upon the highest ureteroscopy-related utilization level that they participate in with levels defined in decreasing order: (6) Hospitalization and ICU care; (5) unplanned hospitalization; (4) unplanned additional operating room or interventional radiology procedure; (3) emergency department (ED) visit; (2) ambulatory encounter: clinic visit; and (1) number of ambulatory patient/provider interactions. Then the rank of each patient in the stent omission arm will be compared to each patient in the stent arm using the unplanned healthcare utilization ranking rules described above such that each pair will have a winner. Summary statistics for the hierarchical composite win ratio endpoint will be presented, including the number of total pairs, and number and proportion of pairs that favor stent omission for each component of the unplanned healthcare utilization outcome. The number of winners and losers for stent omission and corresponding win ratio will be reported with the 97.5% (bootstrapped-based) confidence interval and *p*-value based on the Chi-square statistic. In addition, the probability of a participant with stent omission doing better than a participant with a stent will be presented. It is not expected to have missing data for this endpoint but if there is then multiple imputation will be used. Sensitivity analysis will be conducted with the same analysis in the healthcare utilization modified intent-to-treat (HCUmITT, see Sect. 20c) population to assess the robustness of the effect found in the primary analysis.

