Limitations of the SOUL clinic trial include that it is not blinded, and that the type of stent, duration of stenting, and removal method are left at the discretion of the enrolling surgeon. This pragmatism allows variation which may have an impact on outcomes. However, the pragmatic nature of the study is also a strength as it will allow a greater chance of patient enrollment and participation. The variety of centers in the trial provides a diverse multi-center population. Finally, the patient input on trial design and conduct, with regular patient feedback and engagement, is a major strength.

In summary, the SOUL study is innovative and can be insightful for the scientific community because it provides a real-world assessment of patient outcomes from diverse community and academic centers. The combined randomized and observational cohort design captures the outcomes of patients who decline randomization and was developed in conjunction with patient partners. It offers a comprehensive evaluation of PROs for one of the most common procedures in urology, developed with input from patient partners. It assesses 30-day healthcare utilization using a novel hierarchical rank score (Win Ratio). It uses a web-based intraoperative randomization system that allows randomization to occur just before completion of the surgical procedure. It has a qualitative component: interviews and surveys of both surgeons and patients to understand decisions and preferences around stenting. During peer review, this proposed clinical trial was found to have the potential to be paradigm-shifting as the patient’s voice was being heard and incorporated. Finally, it was noted that successful completion of this scientifically rigorous study will likely positively impact the field of urology and help surgeons and patients make patient-driven informed health care decisions.

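### The population called ITT is not all randomized patients as assigned: it requires a baseline pain questionnaire, even for utilization, and dates eligibility after randomization

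*Protocol article*

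**What the plan says.** The Protocol article, section {20c}, builds the ITT population from consented patients who had ureteroscopy and who "complete a baseline PROMIS® Pain Interference questionnaire and fit the definition of an eligible ureteroscopy at the end of the procedure". The same wording serves the randomized and observational cohorts and does not refer to randomization. The healthcare-utilization modified population (HCUmITT) repeats the baseline-questionnaire condition and adds complete 30-day utilization data.

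This ITT set is primary for both RCT co-primary endpoints in {20a}. For pain: "A linear (ANCOVA) model will be used on the intention to treat (ITT) population to compare the two treatments". For utilization, the win-ratio analysis "in the RCT will use the ITT population and will use the unmatched approach". Section {20c} adds: "For the planned ITT analyses, multiple imputation will be used to address missing data".

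On timing, Sequence generation {16a} says of randomization: "This will take place after the completion of the lithotripsy portion of the procedure and verification of second-stage eligibility by the operating urologist". Sections {16b} and {16c} say the same. The Discussion describes a system that "allows randomization to occur just before completion of the surgical procedure". Section {17a} states: "The operating urologist will need to perform the allocated treatment (stent omission or stent placement) and therefore cannot be blinded".

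**The concern.** There are two separate problems, and their consequences differ.

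**Baseline questionnaire.** Completing it is not among the eligibility criteria in {10}. Under {18b}, if a patient "fails to complete the preoperative PRO survey, they will receive an electronic automated reminder and will be contacted by the MUSIC Coordinating Center". Nothing there stops surgery or randomization. A randomized patient can therefore fall out of a set labelled ITT. For utilization, the patient is lost although the outcome comes from the electronic health record and the RCT analysis has no baseline pain term. For pain, the patient is lost although a missing baseline could be imputed under the method already planned. Because HCUmITT carries the same condition, the planned sensitivity analysis cannot show what the exclusion does.

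**Timing of eligibility.** The definition judges eligibility at a point later than randomization, when the surgeon knows the assigned arm. If any randomized patient were removed at that point, the comparison would no longer be protected by randomization. No planned population consists of everyone randomized, so no planned analysis would reveal it.

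**Working it through.** **1. The plan's own figures, from Sample size {14}.** These reproduce and are not in dispute.

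- Pain: difference 5, SD 10 (standardized effect 0.5), two-sided alpha 0.025, power 90%, two-sample t test. The noncentral t calculation gives 100.56, so 101 per arm as stated, with power 90.1%.
- Day 7–10 non-response of 10%: 101/0.9 = 112.2; the plan uses 112 per arm, 224 in total.
- Loss of 15% between consent and randomization: 224/0.85 = 263.5, so 264 as stated.
- Utilization: probabilistic index 0.67, by the Mann–Whitney (Noether) formula N = (z for 0.9875 + z for 0.90)² / [12 × 0.25 × (0.67 − 0.50)²] = 143.2, so 72 per arm as stated. With 112 per arm the power is 98.5%.

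The two losses allowed for are ineligibility found before randomization and failure to answer at days 7–10. A missing baseline questionnaire among randomized patients is not allowed for.

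**2. Cost of the questionnaire condition.** The document gives no rate of missing baselines. Let m be the assumed share of the 224 randomized. Patients leaving both co-primary analyses = 224 × m. Evaluable for pain per arm = 112 × (1 − m) × 0.9. Utilization per arm = 112 × (1 − m).

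| m (assumed) | Leave ITT | Pain evaluable per arm | Pain power | Utilization power at 0.67 |
|---|---|---|---|---|
| 0% | 0 | 100.8 | 90.1% | 98.5% |
| 5% | 11 | 95.8 | 88.4% | 98.0% |
| 10% | 22 | 90.7 | 86.5% | 97.4% |
| 15% | 34 | 85.7 | 84.3% | 96.6% |

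Pain power is complete-case and uses the plan's t test, not the ANCOVA. It assumes that 10% of the remaining patients still fail to answer at days 7–10. If the same people skip both questionnaires, the extra loss is smaller.

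**3. Direction of the questionnaire condition.** Participant timeline {13} places the questionnaire within the 30 days before surgery, and allocation happens in the operating room. Response therefore cannot depend on the arm, and no differential bias is expected.

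**4. Timing, with the sections side by side.** The order in {16a}–{16c} is lithotripsy, eligibility verification, randomization, then stent placed or omitted. The Discussion puts randomization shortly before the operation ends. The end of the procedure named in {20c} therefore comes after allocation. The document says neither that eligibility is locked at the earlier check nor how often a randomized patient might later be judged ineligible, so no bias can be calculated.

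**The case against.** The best defence of the eligibility wording is that it is only a filter. The definition starts from everyone who consented, and about 15% of them are expected to have an ineligible case. It must also serve an observational cohort that has no moment of randomization. Read this way, it restates the check in {16a}. That reading is plausible and may well be intended. It does not settle the matter, because the stated time point is later than that check and no sentence keeps randomized patients in.

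A reader might infer more: that the plan re-tests eligibility after allocation, or that outcomes could steer exclusions through the open *Other* category in {10}. The documents do not support this. All three allocation sections put verification before randomization. The *Other* category calls for a discussion with the coordinating-center PI within 7 days; it does not say that eligibility is decided then or that outcomes are consulted. Section {11b} provides for exclusion criteria that emerge late, but the consequence it names is stopping surveys, not removal from analysis. No section describes removing a randomized patient.

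A reader might also use the emergency-visit rates in the Background to show a spurious difference. Any such figure is hypothetical: it needs only patients with events to be removed, all from one arm, and that rate is not the co-primary statistic.

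On the questionnaire, the defence is that {18b} plans reminders, personal contact, and telephone or paper completion, so few baselines may be missing. That stands: at 5% missing, pain power falls by only 1.7 points, and utilization power is barely touched. It limits the size of the loss but gives no reason to require a pain score for a utilization endpoint.

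The analysis plan and full protocol are not shown. However, the article itself states these populations; {20c} defers only the imputation details.

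**Conclusion.** The point holds as a correction that should be made; it is not a fatal flaw. The set labelled ITT is not all randomized patients as assigned, for either RCT co-primary endpoint.

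The questionnaire condition is plain in the text. It loses usable patients, power and generalizability, and is not expected to bias the arms. At an assumed 5–15% missing, pain power drops to between 88.4% and 84.3%, while utilization stays above 96% at the design effect.

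The eligibility condition is an ambiguity with a possible bias of unknown size. The text permits exclusion after an unblinded surgeon knows the allocation, but does not show that any such exclusion is planned.

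**What to change.** For the randomized cohort:

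- Define ITT as all randomized patients, analysed in the assigned arm.
- State that second-stage eligibility, including the *Other* category, is fixed at the check before randomization, and that no later reclassification removes a randomized patient from analysis.
- Impute a missing baseline Pain Interference score within the multiple imputation already planned.

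For both cohorts, drop the questionnaire condition from the populations used for utilization, including HCUmITT. Keep the present definition as a sensitivity set.

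The cost is a rewording of the population definitions before data lock, with no new data collection. The downside is that a few patients with a complication recognised late stay in, which slightly dilutes the contrast.

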### Plans to give access to the full protocol, participant-level data and statistical code {31c}

The full study protocol is available to the public at the trial’s public-facing web page: https://www.stentornot.com/study-documents. De-identified patient-level data from the trial will be archived in the PCORI Repository and reasonable requests for secondary use will be considered through standard procedures noted on the PCORI website: https://www.pcori.org/research/about-our-research/data-sharing-maximizing-utility-pcori-funded-data. Statistical code may be shared upon reasonable written request to the trial’s principal investigator.

## Oversight and monitoring

### Composition of the coordinating center and trial steering committee {5d}

SOUL is a patient-centered clinical trial. Its advisory structure reflects this priority through robust involvement of both expert and public/patient partners in every aspect of the trial’s design and conduct. Two groups will serve in ongoing advisory roles to help guide the successful implementation and performance of the trial: an investigative team of physicians, researchers, and other coordinating center staff and a stakeholder engagement group that includes patient partners and advocates in kidney stone disease. The principal investigator has ultimate responsibility for overseeing both the investigative team and the stakeholder engagement group.

The investigative team consists of the principal investigator and co-investigators with expertise in both content (ureteroscopic treatment of kidney stone disease, patient-reported outcomes) and process (pragmatic clinical trial design and management, qualitative assessments of patient and physician preferences) relevant to the study, statistical analysts, project managers, and trial coordinators. They will meet at least monthly for the duration of the trial to review progress, discuss any needed modifications or adaptations, and facilitate ongoing success. A core team of the PI and MUSIC staff conducting the staff will meet weekly to ensure study enrolment and milestones are met.

The Stakeholder Engagement Group is co-led by the principal investigator and one co-investigator (NC), with expertise in stakeholder engagement, and also includes patients with experience of ureteroscopy, patient advocacy organizations, a payor representative, and physicians with experience of executing large scale patient-centered clinical trials. The stakeholder engagement group will meet at least two times annually to discuss study progress, as well as any problems that have been encountered regarding recruitment, enrolment, or retention. As the trial nears completion, we will also discuss dissemination efforts and seek out guidance for assistance with dissemination to the broader community.

In addition to the advisory panels described above, we will also hold annual Full Project Team meetings to include all project investigators, staff, stakeholder engagement group representatives, performance site physician leads, and representatives from PCORI. The primary purpose of these meetings will be to maintain forward progress and address any issues that have arisen.

### Composition of the data monitoring committee, its role, and reporting structure {21a}

Safety oversight is under the direction of a Data and Safety Monitoring Board (DSMB) composed of individuals with the appropriate expertise, including experience of clinical trials for stone surgery patients, and appropriate biostatistics knowledge for clinical trials. Members of the DSMB are independent from the study conduct and free of conflict of interest. The DSMB will meet at least semi-annually to assess safety and efficacy data on each arm of the study. The DMSB will operate under the rules of an approved charter that was written and reviewed at the organizational meeting of the DSMB. The DSMB will provide its input to PCORI through regular reports.

### Adverse event reporting and harms {22}

The principal investigator and co-investigators are responsible for the detection, documentation, grading, and assignment of attribution and expectedness of events meeting the criteria and definition of an adverse event. Adverse events will be collected by review of the electronic health record, ongoing communication with patients and participating performance site clinicians, and a text message query to patients at postoperative day 30. The DSMB will regularly review data on adverse events as a part of their ongoing safety reviews. Adverse events meeting standard criteria for classification as “serious adverse events” will be reported to the governing IRB.

For the purposes of this trial, an adverse event is considered any untoward medical occurrence in a patient receiving study treatment that has or potentially has a causal relationship with this treatment. Any untoward medical occurrences that are unrelated to the study intervention will not be considered adverse events. Symptoms of kidney stone disease and expected side effects from ureteroscopy lithotripsy and stent placement are not considered adverse events for this study.

### Frequency and plans for auditing trial conduct {23}

Each clinical performance site will perform internal quality management of study conduct, data collection, documentation, and completion. Quality control procedures will be implemented beginning with the data entry system and data checks that will be run on the database. Any missing data or data anomalies will be communicated to the performance site for clarification/resolution.

The institutional review board will verify that the clinical trial is conducted, and data are generated, documented, and reported in compliance with the protocol and applicable regulatory requirements.

The performance site will provide direct access to all trial-related sites, source data/documents, and reports for the purpose of monitoring and auditing by the MUSIC coordinating center and inspection by local and regulatory authorities.

### Plans for communicating important protocol amendments to relevant parties (e.g., trial participants, ethical committees) {25}

Any amendment to the study protocol and/or informed consent will require review and approval by the IRB before the changes are implemented to the study. Any such amendments will also be provided to PCORI for review and feedback prior to implementation.

### Dissemination plans {31a}

This study will comply with all applicable PCORI policies, including but not limited to the PCORI Policy for Data Management and Data Sharing and the PCORI Process for Peer Review of Primary Research and Public Release of Research Findings. Trial results will be published in peer-reviewed scientific journals, and a layperson summary of key findings will be made available to the public.

## Discussion

The SOUL trial addresses shortcomings of prior studies by (1) assessing PROs (HRQOL, symptoms, and treatment satisfaction), (2) assessing objective standardized healthcare outcomes, (3) using an integrated trial design in a real-world setting, (4) using RAND Appropriateness Criteria for comparative effectiveness studies, and (5) improving the evidence base on stent decision-making by using a mixed methods approach. Furthermore, the study design was based on a multi-year process whereby we used a participatory action approach from patient partners to ensure we assessed patient-centered outcomes and identified the issue of stenting as a significant problem when undergoing kidney stone surgery.

Furthermore, SOUL leverages the existing interpersonal and professional networks within a surgical quality improvement collaborative (MUSIC) to strengthen and support the trial’s success. All centers used a standardized pain protocol pathway which is a strength of this study. Tri-annual MUSIC consortium-wide meetings are held to discuss data, review risk-adjusted measures of processes of care and patient outcomes, and identify strategies and best practices for quality improvement. We will use this forum to engage with urologists about the SOUL trial as well as regular working group meetings that MUSIC conducts on a tri-annual basis.

As a multicenter prospective trial, the success of the SOUL study will depend on sustained engagement and participation by investigators and site champions across a broad spectrum of urologic practices throughout Michigan and beyond. This will be achieved in part by utilizing the existing sense of community and regular cadence of both in-person and virtual meetings between members of MUSIC. Investigators and other key personnel from multiple trial performance sites can be refreshed about key aspects of the study, provided with progress updates, and recognized for their contributions at collaborative-organized functions. Similarly, issues that may arise at individual performance sites can be efficiently resolved and solutions quickly disseminated to the broader group through existing networks.

Limitations of the SOUL clinic trial include that it is not blinded, and that the type of stent, duration of stenting, and removal method are left at the discretion of the enrolling surgeon. This pragmatism allows variation which may have an impact on outcomes. However, the pragmatic nature of the study is also a strength as it will allow a greater chance of patient enrollment and participation. The variety of centers in the trial provides a diverse multi-center population. Finally, the patient input on trial design and conduct, with regular patient feedback and engagement, is a major strength.

In summary, the SOUL study is innovative and can be insightful for the scientific community because it provides a real-world assessment of patient outcomes from diverse community and academic centers. The combined randomized and observational cohort design captures the outcomes of patients who decline randomization and was developed in conjunction with patient partners. It offers a comprehensive evaluation of PROs for one of the most common procedures in urology, developed with input from patient partners. It assesses 30-day healthcare utilization using a novel hierarchical rank score (Win Ratio). It uses a web-based intraoperative randomization system that allows randomization to occur just before completion of the surgical procedure. It has a qualitative component: interviews and surveys of both surgeons and patients to understand decisions and preferences around stenting. During peer review, this proposed clinical trial was found to have the potential to be paradigm-shifting as the patient’s voice was being heard and incorporated. Finally, it was noted that successful completion of this scientifically rigorous study will likely positively impact the field of urology and help surgeons and patients make patient-driven informed health care decisions.

